### Longitudinal Cohort

Both EPICC and mChoice projects will enroll a cohort of 400 participants. Study participation will range from 12-18 months, depending on the study enrollment date. Eligibility criteria include (1) age 18-39 years, (2) the male sex, (3) ever had sex (as a top or a bottom, insertive or receptive) with a person who has a penis, (4) have an active prescription for PrEP (including both new prescriptions at baseline or refills), (5) receive care at 1 of the participating study sites, (6) provide a mailing address within the 50 states where packages can be received, (7) have daily smartphone access, and (8) be fluent in written and spoken English or Spanish. Cohort participants will be recruited by the clinic staff during scheduled visits, through study advertisements placed in clinic waiting rooms, or through study advertisements on social media platforms.

Each project team builds off prior work to adapt their unique digital health tools poised to support PrEP choice and ongoing adherence. The EPICC project builds from the HealthMpowerment (HMP) intervention. HMP is a theory-based status app designed to provide health and wellness information and resources relevant to young people via a mobile optimized platform. HMP was created based on the Integrated Behavioral Model [22-24]. HMP is flexible and easy to adapt for specific populations and health topics. The EPICC project’s version of HMP includes resources most relevant for our study population. The mChoice app was created based on the Information System Research framework and builds on formative work to develop a PrEP adherence and monitoring app [25-27]. The mChoice app was built in collaboration with Compliance Meds Technologies (CMT) CleverCap. CMT is an mHealth technology solutions provider that develops adaptable technology to promote health. The CleverCap app is linked to a CleverCap device, which is an electronic pill bottle that records when the cap opens and closes and tracks medication adherence. The CleverCap app was customized to the needs of the mChoice project to support PrEP adherence among YMSM. It offers PrEP resources, such as 2 client-facing PrEP training modules created by the study team and a sexual activity log. It can be programmed for the use of participants who are taking any of the 3 PrEP regimens: oral (daily or event driven) or injectable. Table 2 lists the features of each project’s mobile app.

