### Cohort Procedures

Participants will complete a computer-assisted self-interview (CASI) every 3 months while in the study. Surveys will be hosted on REDCap. EPICC surveys will be distributed through emails and links available within the study app. mChoice surveys will be completed at study sites on a tablet. The surveys will address various topics related to PrEP care engagement, PrEP usage, and PrEP adherence, as well as sociodemographics and risk factors related to PrEP adherence (Table S1 in Multimedia Appendix 1) [7,28-38].

EPICC project participants will complete a home-based DBS collection kit every 6 months while in the study to assess for levels of tenofovir-diphosphate (TFV-DP) and emtricitabine-triphosphate (FTC-TP). Additionally, EPICC project participants can attend an optional virtual onboarding visit with a member of the study team to review key features of the study app and DBS collection instructions. mChoice project participants who report using PrEP containing TFV and FTC will provide a urine sample of 15-30 mL at each visit to measure adherence. After the visit, the staff will use the urine sample for a rapid strip test to interpret adherence results. The staff will upload a picture of the test results to REDCap to send to the lab so that they can perform quality control checks. Participants’ urine samples will be used for 2 separate tests: one that measures TFV levels and another that measures FTC levels. Throughout the study period, participants (EPICC and mChoice) will be asked to track their PrEP adherence and sexual behavior in study mobile applications. Electronic health record (EHR) data (EPICC and mChoice Studies) will be collected every 6 months during the study period; variables will include PrEP prescription information, HIV testing, sexually transmitted infection (STI) testing, and results. Clinic site staff will complete medical record abstraction (MRA) using participants’ EHRs every 6 months while in the study. MRA will collect information about PrEP prescriptions, STI testing and results, and HIV testing and results. Table S1 in Multimedia Appendix 1 includes cohort measures.

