### Primary Outcome Measures

The primary outcome for provider training is PrEP familiarity, PrEP beliefs, and intentions to use PrEP measured at pre- and posttraining. The primary outcome for the cohort is PrEP adherence. For the EPICC project, adherence outcomes will be measured by using blood and will be tailored for oral PrEP modality (daily or 2-1-1) and categorized as protective (1) or not protective (0). The protective level of PrEP in the blood is defined as ≥4 doses taken per week, and the not-protective level is defined as <4 doses taken per week. Adherence outcomes for participants on CAB-LA will be determined by the timely administration of injections. The timely administration of the second injection is defined as within +/–1 week of the target date and within +/–2 weeks of the target date for subsequent injections. For the mChoice project, adherence outcomes, as measured by using urine, will be assessed by testing TFV and FTC levels in urine specimens collected from participants who report daily use of PrEP containing TFV and FTC. The mChoice project will also measure adherence by electronic medication monitoring via the CleverCap device, EHR data, and self-report.

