##### Analysis Plan

Baseline participant characteristics will be described for the entire sample and disaggregated by regimen, site/region, ethnicity, level of HIV risk perception, substance use, PrEP experience (naive vs familiar), partner relationship status, and the other variables of interest included in Table S1 in Multimedia Appendix 1.

To determine any differences in discontinuation and nonadherence, we will use Cox proportional hazards to analyze (1) time to first discontinuation and (2) time to first nonadherence by regimen using PrEP adherence measures. To incorporate observations after the first discontinuation or after the first nonadherence, including allowing for the possibility of restarting on PrEP after discontinuation and for periods of nonadherence followed by a period of adherence, we will use a multilevel survival model by including a frailty term in the model to allow analysis of recurrent events [40]. We will follow the same analytic strategy for other dichotomous primary and secondary effectiveness and implementation outcomes. For the composite measure of number of prescriptions (primary implementation outcome), we will fit a multilevel linear or a generalized linear regression model, again using all the time point data available to assess the strength of the associations between the composite measure for the number of prescriptions and the predictor variables. To examine the trajectories of regimens, we will use generalized linear mixed models (GLMMs) and a survival model to assess the time to each regimen switch.

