##### Secondary Outcomes

Similar GLMMs will be used for analyzing secondary outcomes. We will conduct a multigroup comparison in pre- and postintervention differences (the difference-in-difference analysis) using a GLMM by adding the group variable and the group × intervention status interaction (pre- and postintervention) in the GLMM described before. Because the PrEP regimen cannot be randomized, we will use the propensity score method [45] to reduce the between-group bias. We will also examine factors that are associated with the length of time that participants take to change their regimens or associated with the instantaneous rate of change of regimen. Since we will know the date of change of the PrEP regimen (from the EHR data), we will apply a Cox proportion hazard ratio model with time-varying covariates (eg, sexual activity, insurance, side effect) to examine the time to change the regimen.

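### EPICC's time to first nonadherence by regimen checks oral users at 6-monthly blood spots and CAB-LA users at each injection, so checking frequency alone can create a hazard ratio against CAB-LA

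*Protocol article*

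**What the plan says.** The EPICC Analysis Plan in the Protocol article fits Cox models for time to first discontinuation and for "time to first nonadherence by regimen using PrEP adherence measures". It then adds a frailty term so that people who lapse and later resume can contribute recurrent events.

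Two sections define what counts as nonadherence and when it can be seen:

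- **Oral PrEP.** Under Primary Outcome Measures the outcome is binary and read from blood: "The protective level of PrEP in the blood is defined as ≥4 doses taken per week". Under Cohort Procedures, "EPICC project participants will complete a home-based DBS collection kit every 6 months while in the study". The payment schedule under Ethical Considerations agrees, listing collections at baseline and at 6, 12 and 18 months.
- **CAB-LA.** Under Primary Outcome Measures, "Adherence outcomes for participants on CAB-LA will be determined by the timely administration of injections". The second injection has a window of 1 week either side of its target date, and later ones must fall "within +/–2 weeks of the target date for subsequent injections".

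On follow-up, Longitudinal Cohort states: "Study participation will range from 12-18 months, depending on the study enrollment date". The article gives no injection interval. It does not say how the two kinds of measure are aligned in time for the Cox model.

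**The concern.** A time-to-first-event analysis depends on how many times the event could have been recorded. Here an oral user has two or three post-baseline chances to be found nonadherent, the first at month 6. A CAB-LA user is judged at the second injection and at every one after it. If injections fall due more often than every 6 months, the CAB-LA group has more chances to fail and earlier ones. A short oral lapse that the next blood spot does not reflect is never counted.

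Adherence is the cohort's primary outcome, and describing real-world use of the different regimens is a stated aim. A hazard ratio that partly reflects the checking schedule could be read as evidence that people on injections adhere less well.

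**Working it through.** **The plan's own figure.** The article gives no figure for this comparison. EPICC's only directly computable figure is the 5.6% minimum detectable difference. It reproduces as a one-sample test with n = 400 × 0.85 = 340 and a reference rate of 20%: 1.645 × √(0.16/340) + 0.842 × √(0.2556 × 0.7444/340) = 0.0357 + 0.0199 = 5.56%. It does not concern a contrast between regimens, and nothing below depends on it.

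**Inputs from the article.** Blood spots at months 6, 12 and 18; follow-up of 12–18 months; CAB-LA judged from the second injection onward.

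**Assumptions.**
- Injection interval of 1 to 3 months, with 6 months as an equal-frequency control.
- Nonadherence of 5–20%: per check for independent checks, or as a share of time for episodes.
- In the first set of simulations, 25% of 340 participants on injections.
- The same nonadherence process in both regimens, so the true hazard ratio is 1.

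**Step 1: number of checks in 18 months.** Oral: 3. CAB-LA at a 2-month interval, first judged at month 1 or month 2: 9.

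**Step 2: hand calculation with independent checks.** With probability p per check and k checks, P(any event) = 1 − (1 − p)^k. At p = 0.10:

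- Oral: 1 − 0.9³ = 27%.
- CAB-LA: 1 − 0.9⁹ = 61%.
- Ratio of cumulative hazards: 9·ln(0.9) / 3·ln(0.9) = 3, whatever p is.

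With only 12 months of follow-up there are 2 and 6 checks, giving 19% and 47%. The ratio is again 3.

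**Step 3: simulated Cox models** (Efron ties, 18 months, 200 replicates per setting). Hazard ratio, CAB-LA to oral:

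| Injection interval (assumed) | Independent checks | Episodes averaging 2 months | Permanent once begun |
|---|---|---|---|
| 1 month | 6.5–8.7 | 2.8–3.6 | 1.05–1.13 |
| 2 months | 3.1–3.9 | 2.2–2.8 | 0.95–1.08 |
| 3 months | 2.1–2.2 | 1.7–1.9 | 0.99–1.04 |
| 6 months | 0.99–1.06 | 0.96–0.99 | 0.93–1.00 |

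At 2 months, a 2-sided 5% test rejected in 83–100% of replicates in the first two columns. In the permanent column, rejection at 1–3 months was 3–9%.

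**Step 4: longer lapses.** A second simulation used 4,000 per group, injections due at month 1 and then every 2 months, and monthly chances of starting and ending a lapse. Mean lapse length is 1 divided by the monthly recovery chance.

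| Monthly onset | Monthly recovery | Mean lapse (months) | Hazard ratio |
|---|---|---|---|
| 5% | 50% | 2 | 2.35 |
| 3% | 30% | 3.3 | 1.76 |
| 5% | 20% | 5 | 1.71 |
| 2% | 10% | 10 | 1.15 |

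**Step 5: isolating the cause.** The 6-month row changes only the checking frequency. The effect disappears there, with hazard ratios of 0.93–1.06 and rejection of 1–8%.

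**Step 6: recurrent events.** If each failed check counts as an event, the expected counts at p = 0.10 are 9 × 0.10 = 0.9 and 3 × 0.10 = 0.3. The ratio is again 3. A frailty term models differences between people; it does not equalise how often they are checked.

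**The case against.** **The article is condensed.** A fuller plan might summarise CAB-LA adherence by 6-month interval or use interval-censored methods. EPICC already evaluates persistence at 6, 12 and 18 months. That is a fair caution. But this article does fix the model, the two definitions and the blood-spot schedule, and followed as written they produce the mismatch.

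**Dating of injections is not stated.** Nothing says each injection enters the model with an exact date. On record abstraction the article says only: "MRA will collect information about PrEP prescriptions, STI testing and results, and HIV testing and results". This stands, and the point does not need exact dates. It needs only that each injection from the second onward is judged, which is how the outcome is defined.

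**The size is assumed.** The interval, lapse pattern and per-check rates are not in the article. A late injection and fewer than 4 doses a week are different constructs, so equal probability per check is a device for isolating frequency. The blood spot's look-back is not given either; lapses it does reflect are not missed. All of this stands. It limits the size of the effect but not the mechanism.

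**Confounding.** A reader might infer that EPICC's comparison is unadjusted, because mChoice writes "Because the PrEP regimen cannot be randomized, we will use the propensity score method" and EPICC does not. The article does not support that. It is silent on covariates for EPICC's Cox model, which a condensed article may leave to the full plan, and the mChoice sentence belongs to a different project's difference-in-difference analysis.

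**Conclusion.** The point holds as a possible bias that should be removed. As written, the comparison checks oral users every 6 months and CAB-LA users at each injection from the second. If injections are due more often than every 6 months and lapses are intermittent, that alone can yield a hazard ratio above 1 for CAB-LA with no true difference. The plan's own provision for lapse and resumption makes intermittent lapses the relevant case.

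The size is conditional. At an assumed 2-month interval it ranges from about 3–4 for independent checks down to about 1.15 for lapses averaging 10 months. It essentially vanishes if nonadherence never reverses.

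A reader might go further and conclude that the regimen hazard ratio will be biased, or that it is EPICC's headline result. Neither follows: the near-null case rules out the first, and the article names adherence, not a contrast between regimens, as the primary cohort outcome.

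**What to change.** For the cross-regimen comparison only:

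- Score every regimen at the existing 6-, 12- and 18-month points. Oral users keep the blood-spot result. CAB-LA users are scored by whether the most recent due injection fell within the window the article already states.
- Analyse with a visit-based logistic GLMM or, for the first event, a discrete-time complementary log-log model, with regimen as a time-varying factor. Use the same grid for the recurrent-event analysis.
- State how a CAB-LA user is classified at a point where no judged injection has yet fallen due, and confirm the source of injection dates. The plan's own CAB-LA definition already needs those dates.
- Keep injection-by-injection timeliness as a description within CAB-LA.

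The cost is a change to derivation and analysis wording, with no new data collection. The downside is that late injections between grid points are not used in the comparison. The equal-frequency row shows that a common schedule removes the artefact in a Cox model; the visit-based models themselves were not simulated.

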##### Provider Training

Mean scores for the pre- and postadministration of PrEP knowledge items, as well as the mean scores for motivational interviewing familiarity and comfort, will be evaluated for significance of difference using the nonparametric Wilcoxon signed-rank test for hypothesis testing of repeated measurements on a single sample [41].

#### The mChoice Project

##### Sample Size and Power Calculations

Sample size estimation was based on the number of individuals required in order to detect an odds ratio of 1.7 or greater, based on a previous intervention study [42], in the primary outcome measures (PrEP adherence and persistence) before and after the intervention. We used a GLMM [43] with 80% power and a 2-sided test of .05 significance. We estimated the power and sample size by simulating responses based on the following assumptions: 20% attrition postintervention follow-up, an intraclass correlation coefficient of 0.2 across sites, and correlations in the range of 0.3-0.6 of participants’ outcomes at different time points [43]. With these conditions, a sample size of 400 was needed [43].

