### Secondary Outcome Measures

Secondary outcomes for provider training include the feasibility and acceptability of implementing provider training and barriers and facilitators impacting the implementation of new PrEP modalities in clinical practice measured through participant responses during the provider focus group discussions that will occur at the end of the cohort follow-up. The EPICC project cohort’s secondary outcome is persistence measures and will be based on (1) the participant’s self-report of currently taking PrEP (daily or 2-1-1) or having received the last shot of CAB-LA and (2) the participant having an active prescription for PrEP based on study records or drug levels associated with use within a 1-month window at 6 months, 12 months, and 18 months postenrollment. mChoice secondary outcomes will consist of sexual risk behaviors, HIV status, substance use, and outcomes by the initial PrEP regimen, as reported through follow-up assessments and EHR data.

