#### The EPICC Project

##### Sample Size and Power Calculations

The sample size for this study was determined based on feasibility after considering the intended analyses and multiple parameter estimates. With 400 participants, the minimum detectable difference in the PrEP adherence and persistence rates was 5.6%, assuming 15% loss to follow-up and a reference rate of 20%, at 0.80 power with a 1-sided test and 0.05 type I error. For baseline to postintervention analyses, simulation-based results indicated the minimum detectable difference from a baseline rate of 20% was approximately 9% (odds ratio 1.6), assuming again 15% loss to follow-up, at 0.80 power with a 1-sided test and 0.05 type I error [39].

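### mChoice powers a before-after rise in PrEP persistence, although eligibility puts persistence at or near its ceiling at baseline

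*Protocol article*

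**What the plan says.** All references are to the protocol article.

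- **Longitudinal Cohort** (both projects): each participant must "have an active prescription for PrEP (including both new prescriptions at baseline or refills"). Study Design describes the mChoice Aim 1 population as men already using PrEP.
- **The mChoice Project, Sample Size and Power Calculations**: the cohort is sized to "detect an odds ratio of 1.7 or greater" "in the primary outcome measures (PrEP adherence and persistence) before and after the intervention", with "80% power and a 2-sided test of .05 significance", 20% attrition, a site intraclass correlation of 0.2 and within-participant correlations of 0.3 to 0.6. The result is N = 400. No baseline rate is given for either outcome.
- **The mChoice Project, Primary Outcome**: a GLMM compares pre- and postintervention values of each outcome.
- **Primary and Secondary Outcome Measures**: the cohort primary outcome is adherence. For the rest, "mChoice secondary outcomes will consist of sexual risk behaviors, HIV status, substance use, and outcomes by the initial PrEP regimen". Persistence is in neither mChoice list and is defined only for EPICC: self-reported current use, together with an active prescription or compatible drug levels, at 6, 12 and 18 months.
- **Aims and Objectives, Study Design (mChoice Aim 1) and Discussion (Overview)**: an increase in persistence is an aim or an expectation.

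**The concern.** A before-after test of improvement needs people who can move from failure to success. Persistence means staying on PrEP, and the cohort is selected for holding a current prescription. Nearly everyone starts as a success, so the measure can hardly do anything but stay level or fall.

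Two things follow. The stated 80% power cannot describe persistence, although the sample-size section names it as a primary outcome. And if the pre/post model is fitted as planned, ordinary discontinuation appears as a decline from baseline, which a reader could take as an effect of the intervention. As an illustration only, since the article gives no discontinuation rate: if 20% to 40% stopped by 12 months, the contrast would be −20 to −40 points. That is simply the discontinuation rate, with nothing to show whether the intervention raised or lowered it.

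**Working it through.** **Inputs from the article.** OR 1.7; two-sided α = 0.05; power 80%; 400 enrolled with 20% attrition, so 400 × 0.8 = 320 completers; within-person correlation r = 0.3 to 0.6. **Assumption:** the baseline rate p0, which is not stated and is therefore scanned.

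**Formulas** (paired proportions, normal approximation; site clustering ignored)

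- Post rate: p1 = 1.7·o / (1 + 1.7·o), where o = p0/(1 − p0)
- V = p0q0 + p1q1 − 2r·√(p0q0·p1q1), with q = 1 − p
- Power = Φ[(p1 − p0)/√(V/320) − 1.96]
- Enrolment needed = V·[(1.960 + 0.842)/(p1 − p0)]² / 0.8

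**The plan's own figure.** N = 400 can be neither confirmed nor refuted without a baseline rate. This formula needs 264 (r = 0.3) or 153 (r = 0.6) at a 20% baseline, and 686 or 402 at 90%. Treating the two occasions as independent samples gives 380 at 20%. For a mid-range baseline, which adherence may well have, 400 is ample under this approximation.

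**Moving towards the ceiling**

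| Baseline p0 | Post p1 at OR 1.7 | Power, r = 0.3 | Power, r = 0.6 | Enrolment needed (r = 0.3 / 0.6) |
|---|---|---|---|---|
| 20% | 29.8% | 93.2% | 99.5% | 264 / 153 |
| 80% | 87.2% | 83.5% | 97.1% | 365 / 212 |
| 90% | 93.9% | 57.1% | 79.8% | 686 / 402 |
| 95% | 97.0% | 33.5% | 51.5% | 1337 / 788 |
| 99% | 99.4% | 10.2% | 14.5% | 6557 / 3878 |

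Worked line for p0 = 95%, r = 0.3: o = 19; p1 = 32.3/33.3 = 0.96997; difference 0.01997; V = 0.05431; √(V/320) = 0.01303; 0.01997/0.01303 = 1.533; Φ(1.533 − 1.960) = 0.335.

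As a cross-check, a simulation with participant and site random intercepts, a conditional OR of 1.7 and a McNemar test gave 35% to 43% power at a 95% conditional baseline. It gave 67% to 76% at a 20% baseline.

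**At exactly 100%.** The baseline odds are infinite, so no post rate yields OR 1.7 and no N gives power for an increase. A logistic pre/post fit to such data separates: the time coefficient was about −24 to −25 with a standard error of about 12,000.

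**New starters.** New prescriptions are eligible, so some participants may hold one without yet taking PrEP. If 30% were in that position and 80% were taking PrEP later, OR = (0.8/0.2)/(0.7/0.3) = 1.71. The target can then be reached, but through uptake of a prescription already held at entry, not through persistence.

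**EPICC, for comparison.** With 400 × 0.85 = 340 completers, the 5.6-point difference reproduces as a one-sample, one-sided test against a fixed 20%: (0.056 − 1.645·√(0.16/340)) / √(0.256·0.744/340) = 0.858, so power is 80.5%. That test needs no baseline measurement. The separate before-after figure also holds as arithmetic: 0.25 × 1.6 = 0.40, and 0.40/1.40 = 28.6%.

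**The case against.** The strongest reply is that mChoice does not define persistence. The only definition shown, EPICC's, includes self-reported current use, and new prescriptions are eligible. Baseline persistence could then be below 100% and the odds ratio finite. This stands against a claim that persistence is mathematically fixed at entry. It does not rescue the power statement, because the movement it allows is uptake, and without such starters the baseline sits where power is low.

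The definition and model could also be settled in an analysis plan that is not shown. That would answer a complaint of omission. Here, though, the article itself states a power basis and a model that do not fit its eligibility rule.

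Three stronger readings are tempting, and the documents do not support them:

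- **EPICC's power is wrong too.** The article states: "For baseline to postintervention analyses, simulation-based results indicated the minimum detectable difference from a baseline rate of 20% was approximately 9% (odds ratio 1.6"). That sentence names no outcome; adherence and persistence are named in the preceding one, which gives the 5.6-point figure. EPICC scores persistence only after enrolment and already plans Cox and frailty models for discontinuation.
- **HIV status is fixed by eligibility.** None of the eight listed criteria mentions HIV status. Being HIV-negative at entry is a sound inference from PrEP use, but it is not stated, and HIV status was never powered.
- **N = 400 is refuted.** It is not. Adherence is unaffected, and the baseline rate needed to check 400 is not given.

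**Conclusion.** The point holds for mChoice persistence. The before-after odds ratio of 1.7 and its 80% power cannot apply to an outcome that starts at or near its ceiling by selection. Power is about 33.5% to 51.5% at a 95% baseline and 10.2% to 14.5% at 99%; at 100% the comparison has no finite odds ratio. These figures rest on an assumed baseline, on 320 completers, on the plan's correlation range and on a paired normal approximation that leaves out site clustering. The direction of the problem needs only the ordinary meaning of persistence and the prescription criterion.

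Separately, persistence is primary in the mChoice power section and absent from the mChoice outcome lists. That inconsistency is plain in the text and depends on no assumption.

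Two minor points follow. EPICC's before-after sentence should say which outcome its 20% baseline describes, since 20% is not a plausible starting value for persistence in a cohort that all hold prescriptions. And "Similar GLMMs will be used for analyzing secondary outcomes", with HIV status among those outcomes, invites the same separation if everyone is HIV-negative at entry, as is presumably the case.

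**What to change.** - **mChoice power statement:** restrict OR 1.7 and N = 400 to adherence, and state the baseline adherence rate used in the simulation.
- **mChoice persistence:** define it and list it consistently among the outcomes. Take it out of the pre/post GLMM. Report the proportion persisting at follow-up with a two-sided 95% confidence interval, and time to discontinuation from enrolment, as EPICC already plans. If a test is wanted, name an external benchmark in advance. Precision is adequate: at an assumed 70% persisting among 320, the half-width is 1.96·√(0.7 × 0.3/320) = 5.0 points.
- **Aims and Discussion:** reword the intention to increase persistence to match.
- **EPICC:** state that the 20% baseline and OR 1.6 apply to adherence. The 5.6-point figure and the discontinuation models can stand.
- **HIV in mChoice:** report incidence per 100 person-years with an exact Poisson interval in place of a pre/post GLMM.

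The cost is wording in the power, outcome and analysis sections, with no new data collection. The real price is inferential: without a baseline contrast or a control group, the persistence result is descriptive or benchmarked and cannot be presented as a demonstrated increase.
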